# Impact of an Education Training Package to Anganwadi Workers for Improving Oral Health Knowledge Among Mother-Child Dyads in Kerala, India: Protocol for a Mixed Methods Implementation Study

**DOI:** 10.2196/91171

**Published:** 2026-05-08

**Keywords:** community health workers, oral health, implementation science, India, preschool child

## Abstract

**Background:**

Maternal and child oral health remains a significant public health concern in India, contributing to early childhood caries, adverse pregnancy outcomes, and long-term health complications. Anganwadi workers (AWWs), under the Integrated Child Development Services Scheme (ICDS), are well positioned to promote preventive oral health behaviors. However, oral health education is not part of their core training. This protocol outlines an implementation research study to develop, deliver, and evaluate a contextualized oral health education training package through AWWs for mother-child dyads in Kochi, Kerala.

**Objective:**

The objectives of this study are to (1) assess the current oral hygiene knowledge, attitude, and behavior and identify barriers and facilitators for implementing the oral health education training package among AWWs, parents, and other key stakeholders; (2) evaluate the oral health education training package for coverage, acceptability, adoption, fidelity, and scalability; and (3) assess the impact of an oral health education training package on the improvement in oral health knowledge, attitude, and behavior among mothers.

**Methods:**

A mixed methods implementation study will be conducted across 100 Anganwadi centers in 3 phases following the Exploration, Preparation, Implementation, and Sustainment framework. Phase 1 will assess baseline oral hygiene practices and identify contextual barriers and facilitators using structured questionnaires and qualitative interviews. In phase 2, AWWs will be trained using a structured oral health education package and will deliver oral health messages to mother-child dyads during routine sessions. Implementation outcomes—acceptability, coverage, adoption, fidelity, and scalability—will be evaluated using observation checklists and program tracking tools. Phase 3 will assess the impact by evaluating changes in maternal oral health knowledge, attitude, and behavior through preintervention and postintervention questionnaires administered to a subsample of mothers. Dissemination of findings and planning for long-term integration into ICDS will also be undertaken.

**Results:**

The study obtained funding in May 2024. The data collection commenced in April 2025. A total of 101 Anganwadi centers have been enrolled. Permissions, stakeholder meetings, baseline data collection, preparation of the teaching module, and training of AWWs (September 2025) have been completed. Follow-up visits to assess implementation parameters are ongoing. Data collection is expected to be completed in April 2026, followed by data analysis in May 2026 and dissemination by July 2026.

**Conclusions:**

This study is expected to generate practical insights into the feasibility of integrating oral health education into ICDS through AWWs. The intervention will be embedded within existing ICDS touchpoints and supported by centralized training, travel allowances, and regular supervision. Findings are expected to inform a scalable, community-based model aligned with national policy priorities for oral health promotion.

**Trial Registration:**

Clinical Trial Registry of India CTRI/2025/07/090759; https://tinyurl.com/32yu6avz

**International Registered Report Identifier (IRRID):**

DERR1-10.2196/91171

## Introduction

Oral health is essential for overall health, and poor oral hygiene can lead to various oral diseases, affecting both children and adults [1-3]. Maternal and child oral health is of particular concern as it plays a crucial role in early childhood development and sets the foundation for long-term oral health. Maternal oral health has been linked to adverse pregnancy outcomes, such as preterm birth, low birth weight, and increased risk of early childhood caries (ECC) in children [4]. ECC, a preventable disease, affects infants and toddlers, causing pain, infections, and long-term dental problems. Poor oral health in early childhood can impact a child’s growth, nutrition, speech development, and school performance [5]. Oral health and nutrition are closely linked in early childhood, as dietary habits affect both growth and dental development. Poor nutrition, particularly high sugar intake and inappropriate feeding, increases the risk of ECC and impacts overall health [6,7]. Thus, addressing maternal and child oral health is crucial for promoting well-being and reducing the burden of oral diseases.

Despite the burden, inequity exists in the availability and accessibility of professional oral health services. Oral care at the grassroots level is limited, necessitating the need for task shifting to less specialized health care workers by providing appropriate training and supervision [1]. Anganwadi workers (AWWs) are community-based health workers under the Integrated Child Development Services Scheme (ICDS) of the Government of India. They are primarily women selected from the local community and are trained to deliver maternal and child health care services at the grassroots level. In addition to educating children and mothers at the designated Anganwadi centers (translated as courtyard shelters), they also provide prenatal and postnatal education through home visits and conduct regular health checkups for pregnant women. They monitor the growth and development of children aged younger than 6 years. As of 2023, there were approximately 1.34 million AWWs in India [8]. They have a unique opportunity to reach mothers and children in rural and underserved areas, where access to dental care may be limited, and can play a key role in delivering oral health education interventions. Integrating oral health education with the regular nutrition and health sessions conducted by AWWs under ICDS provides a feasible, sustainable approach to reduce ECC and promote healthy growth [9,10]. Similar studies have shown that such interventions contributed to improved oral health knowledge, attitudes, and behaviors among mothers and children, as well as improved use of dental services [11-13].

Despite this evidence, oral health has historically received limited attention in national health agendas and policies [14]. Only in recent years has it begun to gain recognition as an integral component of overall health and well-being. The National Oral Health Program (NOHP) was piloted in 1999. However, it was in 2013 that the program was revamped to its present form [15]. One of the activities under NOHP includes oral health promotion through training of dental and paradental health functionaries in the health care delivery system. Anecdotal evidence suggests that the NOHP is yet to be fully implemented in Kerala, with the current focus being more on setting up dental health care units. It is not well established whether AWWs have received standardized or formal training for oral health promotion [16,17].

Few studies have explored the effectiveness of oral health promotion by AWWs in India [16-20], but the focus on implementation parameters has been limited. This study addresses a critical gap by evaluating a model for integrating oral health into community-based maternal and child health services through Anganwadi centers**.** This study is an implementation research project aimed at evaluating the feasibility and implementation of an oral health education training package delivered through AWWs using the Exploration, Preparation, Implementation, and Sustainment (EPIS) framework. Changes in oral health knowledge among mother-child dyads will be assessed as secondary exploratory effectiveness outcomes. The objectives of this implementation research are as follows:

To assess the current oral hygiene knowledge, attitude, and behavior and identify barriers and facilitators for implementing the oral health education training package among AWWs, parents, and other key stakeholdersTo evaluate the oral health education training package for coverage, acceptability, adoption, fidelity, and scalabilityTo assess the impact of an oral health education training package on the improvement of oral health knowledge, attitude, and behavior among mothers

## Methods

### Study Design

This implementation science project adopts a sequential mixed methods design and will be conducted in 3 distinct but interrelated phases. The overarching aim is to develop, implement, and evaluate a contextualized oral health education training package for AWWs in India.

This implementation research is guided by the EPIS framework—exploration, preparation, implementation, and sustainment [21]—which provides a structured approach for adopting evidence-based practices within real-world systems (Figure 1). The study will be undertaken in 3 phases: formative assessment and customization of the training package (phase 1), implementation and process evaluation of the training package (phase 2), and impact assessment and dissemination for scaling up (phase 3).

**Figure 1 figure1:**
[figure not shown]
Study framework. EPIS: Exploration, Preparation, Implementation, and Sustainment; IEC: information, education, and communication.

### Study Setting

The study will be implemented in Anganwadi centers in Kochi, Kerala, India.

### Participants and Eligibility

Participants will be recruited across 3 study phases and will include AWWs, ICDS supervisors, Child Development Project Officers (CDPOs), and mothers or caregivers of children enrolled in Anganwadi centers. The inclusion criteria for each group are presented in Textbox 1.

Inclusion criteria for study participants.
**Anganwadi workers**
Anganwadi workers currently working at Anganwadi centers located within the Kochi Urban III administrative region and expected to continue serving in the study centers during the study period
**Mothers or caregivers**
Mothers or primary caregivers whose preschool children (aged 1-6 years) are enrolled beneficiaries of any Anganwadi center in Kochi Urban III administrative region and who are able to attend Anganwadi sessions and provide informed consent
**Child Development Project Officers (CDPOs)**
CDPOs currently working in Ernakulam District who oversee sectors included in the study
**Integrated Child Development Services Scheme (ICDS) supervisors**
ICDS supervisors currently supervising the selected Anganwadi centers within the Kochi Urban III administrative region

### Implementation Framework

The EPIS framework will be incorporated during the various phases of the study. Phase 1 aligns with exploration and preparation, phase 2 corresponds to implementation, and phase 3 aligns with sustainment.

#### Phase 1: Formative Assessment and Customization of the Training Package (Exploration and Preparation)

Dental diseases in childhood, especially ECC, are a major public health concern globally [22]. In India, nearly half of all children are affected, and in Kerala, ECC prevalence among preschoolers ranges from 44% to 53% [22,23]. This underscores the urgent need for preventive interventions at the early childhood stage. However, information is limited on both AWWs’ knowledge of oral health and that of the children’s parents and caregivers.

The objective of this phase is to assess existing oral hygiene knowledge, attitude, and behavior and implementation readiness through surveys, interviews, and focus group discussions (FGDs) with mothers, AWWs, and ICDS officials (CDPOs and ICDS supervisors).

Findings obtained from the exploratory stage will guide the preparatory stage, which involves cultural and linguistic adaptation of the NOHP oral health manual. This will include developing and customizing training and information, education, and communication (IEC) materials, as well as formulating a context-specific implementation plan for this oral health education training package. The manual covers key aspects of oral health, including common oral diseases and their prevention in home and professional settings, management strategies for oral diseases, handling dental emergencies, debunking common myths, sharing facts about dental health, and interactive activities to reinforce learning and understanding of concepts.

#### Data Collection in Phase 1

Quantitative and qualitative methods will be used to achieve these objectives, including questionnaires, in-depth interviews, key informant interviews, and FGDs with stakeholders such as AWWs, government officials, and mothers, parents, and caregivers of children. In the quantitative phase, a pretested questionnaire developed from previous literature [24-27] will be used to assess current oral hygiene knowledge, attitude, and behavior among purposively selected parents and caregivers, and the results will be analyzed descriptively.

In the qualitative phase, purposive sampling will be used. Separate in-depth interview guides and FGD guides will be developed for each participant group, including AWWs, mothers, ICDS supervisors, and CDPOs (administrative officers). FGDs will be conducted with AWWs and mothers until theoretical saturation is reached. In-depth interviews will be carried out with mothers and AWWs, while key informant interviews will be conducted with CDPOs and ICDS supervisors of the selected Anganwadi centers. All qualitative data will be audio-recorded, transcribed, translated, and thematically analyzed using a deductive approach.

Findings from both phases will be used to customize the training manual on oral health promotion for health workers developed by the Centre for Dental Education and Research, All India Institute of Medical Sciences (AIIMS), for the NOHP, Ministry of Health and Family Welfare, Government of India [28] and to formulate an implementation plan to guide the structured delivery of the oral health training and education package. A contextualized training module for AWWs and a structured implementation plan detailing strategies for training delivery, monitoring, and integration into existing ICDS activities are expected to be achieved at the end of this phase.

#### Phase 2: Implementation and Process Evaluation of the Training Package (Implementation)

The focus is on training AWWs at the center level. Each Anganwadi center is staffed by one AWW and an assistant or helper; hence, implementation will be evaluated at the center level, with the AWW as the primary delivery agent.

The training package developed in phase 1 will be delivered by dental professionals or health personnel from the local health department. Each AWW will participate in a structured interactive session using PowerPoint presentations, demonstrations, and other teaching aids. IEC materials—including an oral health manual, display posters, and tooth models—will be provided to every Anganwadi center. Following the training, AWWs will be encouraged to integrate oral health education into their regular interactions with children, mothers, and expectant mothers. Flexibility will be allowed in how sessions are conducted so that AWWs can adapt delivery to their existing schedules and community context.

Evaluation of the oral health education training package will be done for coverage, acceptability, adoption, fidelity, and scalability over 6 months (Table 1).

**Table 1 table1:** Monitoring and evaluation framework.

Outcome	Definition or measure	Assessment	Indicator
Acceptability	Attendance: proportion of AWWs^a^ attending the training program Willingness: proportion of Anganwadi centers initially agreeing to participate	Attendance sheet Consent form	Attendance: good (>75%), fair (25%-75%), and poor (<25%) Willingness: good (>75%), fair (25%-75%), and poor (<25%)
Coverage	Proportion of Anganwadi centers implementing the training package by conducting at least one session of a minimum of 30 min, validated through field assistants’ visits to the centers on the scheduled day of training or by reviewing video recordings of the sessions submitted by the AWWs	Field assistants’ direct visits to the Anganwadi centers on the scheduled day of training Ongoing contact with the AWWs Review of video recordings of the sessions submitted by the AWWs	Good: >70% of centers Average: 20%-70% of centers Poor: <20% of centers
Adoption	Proportion of Anganwadi centers conducting more than one training session within 6 mo	Documents (registers and/or videos)	Good: >50% of centers conduct multiple sessions Average: 25%-50% of centers conduct multiple sessions Poor: <25% of centers conduct multiple sessions
Adoption	Total number and duration of sessions conducted by each center	Number, hours	—^b^
Fidelity	Proportion of Anganwadi centers adhering to the training module as originally outlined in the manual and training sessions	Direct observation by field assistants	Good: >50% of centers Poor: <50% of centers

^a^AWW: Anganwadi worker.

^b^Not applicable.

#### Phase 3: Impact Assessment and Dissemination for Scaling Up

This phase focuses on evaluating and sharing the outcomes of the implemented training package. The objective is to assess improvements in oral health knowledge, attitude, and behaviors among mothers and caregivers, and to disseminate these findings to stakeholders. Analysis of preintervention and postintervention oral health knowledge, attitude, and behavior scores will be conducted using the questionnaire used in phase 1 from a subsample of beneficiaries from each Anganwadi center.

The study findings will be disseminated to multiple stakeholders through summary briefs and oral presentations to state-level and district-level ICDS officials—such as the ICDS District Officer, CDPOs, and ICDS supervisors—to support integration of the oral health education training package into routine ICDS activities. Outputs will also be shared with AWWs through local feedback sessions at the sector level, providing practical recommendations for sustaining oral health education within their existing schedules.

### Sample Size

A total of 101 Anganwadi centers in the Kochi Urban III administrative region that include the field practice area of the implementing institution, will be selected. Each Anganwadi unit typically covers about 1000 people, of whom about 15 to 30 are children. The intended beneficiaries of the project would be approximately 1500 to 3000 children and their mothers directly, and about 6000 family members indirectly. The Anganwadi centers hold regular contact sessions (at least twice monthly) with the mothers and families of these children. Thus, the project envisions improving awareness and practices in oral health as a cascading effect from AWWs to children and mothers and ultimately to their families and community.

For the assessment of change in oral health knowledge among mothers, a subsample of approximately 10% of mothers of enrolled children will be selected for the pre-post assessment. This sample size is expected to be sufficient to detect a moderate improvement in knowledge scores (effect size approximately 0.4-0.5) with 80% power at a 5% significance level in paired measurements. As participants are clustered within Anganwadi centers, the analysis will account for clustering using cluster-adjusted statistical methods (eg, mixed effects models or cluster-robust SEs).

### Data Analysis

Data analysis will be undertaken in line with the sequential mixed methods design of the study, with quantitative and qualitative findings analyzed separately and subsequently integrated to inform intervention adaptation and refinement of implementation strategies.

#### Phase 1

Descriptive statistics will be used to summarize participant baseline characteristics and outcome measures. Continuous variables, such as oral health knowledge, attitude, and behavior scores, will be reported as means and SDs or medians and IQRs, as appropriate. Qualitative data will be transcribed verbatim, translated where required, and analyzed using a thematic analysis approach. Coding will be conducted iteratively, with themes developed across stakeholder groups. Data will be managed using QDA Miner Lite (Provalis Research).

#### Phase 2

Implementation outcomes, including coverage, acceptability, adoption, fidelity, and scalability, will be calculated based on criteria described in Table 1 and expressed as frequency and percentages.

#### Phase 3

To evaluate changes between preintervention and postintervention assessments, linear mixed effects regression models will be used. Time (preintervention assessment vs postintervention assessment) will be included as a fixed effect. Random intercepts will be specified for both Anganwadi centers and individual participants to account for clustering of participants within centers and within-participant correlation arising from repeated measurements. Maternal age, education level, and occupation variables will be included as fixed effects where appropriate to adjust for possible confounding. Knowledge, attitude, and behavior scores will be analyzed as separate outcome variables. Missing data will be assessed for extent and pattern. Mixed effects models allow the inclusion of participants with incomplete outcome data under the missing at random assumption. If substantial missing data are observed, sensitivity analyses using multiple imputation will be considered. Effect estimates will be reported with 95% CIs, and statistical significance will be set at *P*<.05. Analysis will be done using SPSS software (version 22; IBM Corp).

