### Training Content and Knowledge Gaps

Oral health education is not part of the core ICDS training, and AWWs differ in their baseline knowledge, public communication skills, and confidence levels. Therefore, variability in how they deliver oral health messages to mothers is anticipated. These differences emphasize the need for a user-friendly, linguistically appropriate, and visually rich training manual. The project uses the official training manual of the NOHP, developed by the Ministry of Health and Family Welfare, incorporating simplified and regionally contextualized content. This approach is supported by evidence from a study conducted in Bihar [30] that found that well-trained frontline workers were more likely to deliver essential services effectively.

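### The Phase 3 random-intercept model leaves the pre-post change unadjusted for center clustering, so its confidence intervals will be too narrow if change varies between centers

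*Protocol article*

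**What the plan says.** The protocol article sets out the Phase 3 model under Data Analysis. "Time (preintervention assessment vs postintervention assessment) will be included as a fixed effect". On the random part it says: "Random intercepts will be specified for both Anganwadi centers and individual participants to account for clustering of participants within centers and within-participant correlation". Maternal age, education and occupation may be added as fixed effects. Each of the three scores is modeled separately, and on inference the article says "Effect estimates will be reported with 95% CIs, and statistical significance will be set at" P<.05. It gives no center-by-time term, no random slope and no robust variance.

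The Sample Size section makes the broader promise that "the analysis will account for clustering using cluster-adjusted statistical methods (eg, mixed effects models or cluster-robust SEs". Robust standard errors appear there only as an example, and the Phase 3 paragraph does not take them up.

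Three other places bear on whether change may differ by center:
- The Phase 2 section says that each center has one worker, who is the main delivery agent and is free to adapt the sessions.
- The Discussion, under Training Content and Knowledge Gaps, says that "variability in how they deliver oral health messages to mothers is anticipated".
- The Results section reports that 91 of the 101 enrolled workers completed training.

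**The concern.** A center random intercept describes how far all scores in a center sit above or below average. It handles correlated levels. The estimate reported here is a change, and what matters for its precision is whether changes are correlated within a center. Mothers at one center share one worker, so a center with good delivery may move all of its mothers more than a center with poor delivery. The planned model has no term for that. A reader told that clustering has been accounted for would take the 95% intervals for the three changes as cluster-adjusted when they are not.

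**Working it through.** **Inputs.** From Sample Size: 101 centers, 15 to 30 children per center, 1500 to 3000 children with their mothers, and a subsample of about 10%. That gives about 150 to 300 mothers, or m = 1.5 to 3 per center. Also from Sample Size: effect size 0.4 to 0.5, "with 80% power at a 5% significance level in paired measurements" (taken as two-sided). The ICC of change, ρ, is not in the documents. I assume 0.05 to 0.30 and show 0 as well.

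**1. The plan's own figure.** For paired data, n = ((1.960 + 0.842)/d)². This gives 50 at d = 0.4 and 32 at d = 0.5. If the effect size is instead on the raw-score SD with zero pre-post correlation, n doubles to 99 and 63. All are below 150, so the claim that the subsample suffices is reproduced. Power at 150 mothers and d = 0.4 is 99.8% (93.4% on the raw-score reading).

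**2. What the planned model does.** Write the score of mother j in center i at time t (0 or 1) as

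y = μ + βt + c_i + p_ij + e_ijt.

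Her change is d_ij = β + (e_ij1 − e_ij0). The center term c_i and the mother term p_ij have both gone. With N complete pairs, the model's standard error for β is √(Var(d)/N), the paired standard error that ignores centers. Covariates that are constant within a mother and enter as main effects do not alter this.

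**3. Numerical check.** One data set was simulated with 101 centers, 3 mothers each and ρ = 0.20, and the planned model was fitted. Its standard error for time was 0.05767; the plain paired standard error was also 0.05767.

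**4. What the standard error should be.** If each center has its own change, d_ij = β + s_i + (e_ij1 − e_ij0) and ρ = Var(s)/Var(d). Then

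Var(mean d) = (Var(d)/N) × [1 + (m − 1)ρ].

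The correct standard error is √(1 + (m − 1)ρ) times the planned one. Actual coverage of the planned interval is 2Φ(1.96/√(1 + (m − 1)ρ)) − 1.

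| m | ρ | 1 + (m − 1)ρ | SE ratio | Coverage | 1 − coverage |
|---|---|---|---|---|---|
| any | 0 | 1.000 | 1.000 | 95.0% | 5.0% |
| 1.5 | 0.05 | 1.025 | 1.012 | 94.7% | 5.3% |
| 1.5 | 0.10 | 1.050 | 1.025 | 94.4% | 5.6% |
| 1.5 | 0.20 | 1.100 | 1.049 | 93.8% | 6.2% |
| 1.5 | 0.30 | 1.150 | 1.072 | 93.2% | 6.8% |
| 3 | 0.05 | 1.100 | 1.049 | 93.8% | 6.2% |
| 3 | 0.10 | 1.200 | 1.095 | 92.6% | 7.4% |
| 3 | 0.20 | 1.400 | 1.183 | 90.2% | 9.8% |
| 3 | 0.30 | 1.600 | 1.265 | 87.9% | 12.1% |

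Simulation at m = 3 (5000 trials per setting) gave coverage of 93.6%, 92.3%, 90.4% and 88.5% for ρ = 0.05, 0.10, 0.20 and 0.30. A center-level analysis of the same data covered 94.8% to 95.0%.

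Centers cannot supply 1.5 mothers. With 51 centers giving one and 50 giving two, the effective m is (51×1 + 50×4)/151 = 1.66. Simulated test error there was 5.6%, 6.4% and 7.2% at ρ = 0.10, 0.20 and 0.30, slightly above the m = 1.5 rows.

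**5. Is a positive ρ plausible?** As an illustration, assume that 30% of centers show no change and the rest improve by 0.5 SD of change. The between-center variance is 0.3 × 0.7 × 0.5² = 0.0525, about 5% of the variance of change. Table 1 would still rate coverage as good with just under 30% of centers holding no qualifying session.

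**6. Power after correction.** At d = 0.4 on the SD of change and ρ = 0.30, power is 99.5% with 150 mothers (m = 1.5) and above 99.9% with 300 (m = 3). On the raw-score reading it is 89.8% and 97.2%. All exceed 80%.

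**The case against.** The strongest reply accepts the algebra and disputes its weight.

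- **The narrowing is conditional.** A reader might infer that the intervals are certainly too narrow. The documents do not support that. They give no ICC of change, and at zero the planned intervals are right. This stands.
- **Exact equality needs complete pairs.** The plan keeps mothers with incomplete outcomes, and for them the intercepts do not cancel entirely. This stands as a qualifier. Between-center variation in change would still be unmodeled.
- **The 12% figure is an extreme.** A reader might infer a false-positive rate of 12%. That figure needs the largest cluster size and the largest assumed ICC together. It also needs an average effect of zero while centers truly differ in their change. If variable delivery is the cause, a package that helps nobody produces no such variation. Undercoverage around a real effect is the better-supported harm.
- **Little hangs on it.** The Introduction calls the changes in oral health knowledge secondary and exploratory. The Discussion calls the study a pilot. The Dissemination section ties the scale-up proposal to favorable implementation outcomes, which are percentages. This lowers the severity. It does not remove the point, because assessing impact on mothers is still the third objective and is tested at P<.05.
- **Leave it to a fuller analysis plan, or rely on the robust standard errors already mentioned.** This does not stand. The article commits to a specific random-effects structure and gives it a purpose that it does not serve. Robust standard errors are only an example elsewhere.

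**Conclusion.** The point holds, with minor to moderate severity. As written, the Phase 3 model does not account for center clustering of the change it reports. For complete pairs this is exact and needs no assumption about the ICC.

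The consequence is conditional. If change varies between centers and centers supply more than one mother, the intervals are too narrow. Over an assumed ICC of 0.05 to 0.30 and about 1.5 to 3 mothers per center, the correct standard error is about 1% to 26% larger than the reported one. Coverage runs from about 94.7% down to 88%, which corresponds to a nominal test error of about 5.3% to 12%. The protocol's account of one worker per center, expected differences in delivery and incomplete training makes some variation likely but does not say how much.

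A reader might also infer that the study is underpowered, that the estimated changes are biased, or that failing to estimate the between-center spread of benefit is an error. None of these follows. Power stays above the stated 80%, point estimates are essentially unaffected, and the spread is not among the stated objectives.

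**What to change.** Change the Phase 3 model before the analysis planned for May 2026, in one of three ways:

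1. Add a random slope for time by center (a center-by-time random effect) to the planned model. In SPSS MIXED this is an intercept and a time effect with center as subject, alongside the participant intercept. In a check on complete pairs it held test error at 4.0% to 5.1%. With few mothers per center, the slope variance will be imprecisely estimated.
2. Analyze each mother's change score with center-clustered standard errors, which the Sample Size section already allows.
3. Test the center-mean changes. This is stable with so few mothers per center. If numbers per center differ, it estimates the average over centers rather than over mothers, and the text should say so.

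Reword the clustering sentence to match the choice. The cost is a line of syntax, a sentence of text and slightly wider intervals, with no new data. Reporting the between-center SD of the change would be a useful optional extra for an implementation study, not a correction.
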